**Developing a causal model using directed acyclic graphs (DAGs) to both identify and summarise causal pathways.**

1. Potential confounders will be determined by the above-named authorship team (a quorum of specialists with expert knowledge). All potential confounders are pre-exposure or at exposure.
   1. Covariates to be included in the selection model:
      1. Type of hypertension (gestational hypertension, chronic hypertension, preeclampsia)*
      2. Maternal diabetes mellitus (yes/no)*
      3. Plurality (1/2+)*
      4. Pre-existing renal disease
      5. Pre-existing autoimmune disease
      6. Maternal smoking during pregnancy
      7. Maternal body mass index
      8. IVF/ART conception
      9. Maternal socioeconomic status (SEIFA quintile)
      10. Maternal age at delivery
      11. Mode of birth (neonatal outcomes only)

*Variables denoted with * are included in the Giant PANDA randomization algorithm.*

**Causal pathway and confounding** (excerpt from Causal Inference, What if. M Hernan & J Robins p85: <https://www.hsph.harvard.edu/miguel-hernan/causal-inference-book/>)

*“...the bias has the same structure: it is due to the presence of a cause (known covariate L or unknown covariate U) that is shared by the treatment A and the outcome Y, which results in an open backdoor path between A and Y. We refer to the bias caused by shared causes of treatment and outcome as confounding…”*

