**PART ONE: DESCRIPTIVE ANALYSIS**

1. **Flow chart of participants**

Total number in cohort > number of linked records > number of hypertensive pregnancies exposed to labetalol or nifedipine.

**Exclusion criteria:** Use of both labetalol and nifedipine prior to 11 weeks’ gestation (unable to be randomized).

1. **Population characteristics to be described for:**
   1. Overall cohort
   2. Women using labetalol during pregnancy and their child(ren)
   3. Women using nifedipine during pregnancy and their child(ren)

| **Variable** | **Overall** | **Labetalol-Exposed** | **Nifedipine-Exposed** |
| --- | --- | --- | --- |
| **Maternal Baseline Characteristics** | | | |
| Maternal age (mean, SD)  *Missing (%)* |  |  |  |
| Maternal age >35 (%) |  |  |  |
| Marital status (%)  *Married/de facto*  *Single*  *Divorced*  *Widowed*  *Missing* |  |  |  |
| Parity (%)  *Nulliparous*  *Multiparous*  *Missing* |  |  |  |
| Hypertensive diagnosis (%)  *Chronic hypertension*  *Gestational hypertension*  *Preeclampsia* |  |  |  |
| Gestation at commencement of treatment (%)  *11^+0^ – 19^+6^ weeks*  *20^+0^ – 27^+6^ weeks*  *28^+0^ – 36^+6^ weeks* |  |  |  |
| Conception via assisted reproductive technology (%) |  |  |  |
| Body mass index (mean, SD)  *Missing (%)* |  |  |  |
| Body mass index ≥ 30 (%) |  |  |  |
| Maternal pre-existing comorbidities (%)  *Type 1 or 2 diabetes mellitus*  *Autoimmune disease*  *Renal disease*  *None* |  |  |  |
| Gestational diabetes mellitus (%)  *Yes*  *No*  *Missing* |  |  |  |
| SEIFA quintile (%)  *1 (most disadvantaged)*  *2*  *3*  *4*  *5 (least disadvantaged)*  *Missing* |  |  |  |
| **Neonatal Baseline Data** | | | |
| Sex (%)  *Male*  *Female*  *Missing* |  |  |  |
| Mode of birth (%)  *Elective caesarean section*  *Emergency caesarean section*  *Instrumental birth (forceps or vacuum)*  *Spontaneous vaginal birth*  *Missing* |  |  |  |
| Gestational age at birth (mean, SD)  *Missing* |  |  |  |
| Birthweight (mean, SD, centile)  *Missing (%)* |  |  |  |
| Plurality (%)  *Singleton*  *Twins or higher order births*  *Missing* |  |  |  |
| **Maternal Outcome Data** | | | |
| Maternal mortality (%) |  |  |  |
| Eclampsia (%) |  |  |  |
| HELLP Syndrome (%) |  |  |  |
| Stroke (%) |  |  |  |
| Cortical blindness (%) |  |  |  |
| Retinal detachment (%) |  |  |  |
| Pulmonary oedema (%) |  |  |  |
| Placental abruption (%) |  |  |  |
| Liver rupture (%) |  |  |  |
| Dialysis (%) |  |  |  |

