**Target Trial Emulation**

| **(A) Research Question** | ***What is the causal effect of exposure to nifedipine on adverse maternal and neonatal outcomes, compared with exposure to labetalol?*** | |
| --- | --- | --- |
|  | **Target Trial (Giant PANDA)** | **Emulation** |
| **(B) Populations** | All women with hypertensive disorders of pregnancy (chronic hypertension, gestational hypertension, or preeclampsia) requiring antihypertensive medication at gestational age 11^+0^-19^+6^; 20^+0^-27^+6^; and 28^+0^-36^+6^.  *Exclusions:* contraindication to labetalol or nifedipine; on both labetalol and nifedipine prior to randomization; unable to provide informed consent; unable to be randomized. | All women with hypertensive disorders of pregnancy (gestational hypertension, chronic hypertension, or preeclampsia) requiring antihypertensive treatment (dispensed labetalol or nifedipine) between 11^+0^ and 36^+6^ weeks’ gestation.  *Exclusions:* Taking both labetalol and nifedipine prior to 11 weeks’ gestation. |
| **(C) Treatment strategies** | Primary  Intention-to-treat (ITT): All women randomized to labetalol or nifedipine, regardless of discontinuation or crossover of treatment groups.    Sensitivity  Per-protocol: All women randomized to labetalol or nifedipine, who continued with assigned treatment until no longer indicated.  On-treatment: All women randomized to labetalol or nifedipine, who continued with assigned treatment until no longer indicated and who self-reported ≥90% adherence across all study contacts. | Primary  Intention-to-treat (ITT): All women who received ≥1 prescription and dispensation of labetalol or nifedipine, including those who received both medications during the study period (crossover will be determined by timing of dispensation) and those who discontinued treatment.  *Crossover defined as receiving both labetalol and nifedipine between 11-36 weeks’ gestation.*  Sensitivity  Per-protocol: All women who received ≥1 prescription and dispensation of labetalol or nifedipine during the study period, but did not receive both medications at any time. |
| **(C) Assignment procedures** | Randomized at diagnosis of hypertension requiring medical intervention (1:1 ratio of nifedipine/labetalol). | “Randomized” (via inverse probability weighting) at point of first dispensation of labetalol or nifedipine during the study period (≥11 weeks’ gestation and ≤36+6 weeks’ gestation). |

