| **(D) Follow-up period** | From 11 weeks’ gestation until 28 days post-birth. | From 11 weeks’ gestation until 28 days post-birth. |
| **(E) Outcomes** | **Primary Maternal**  Severe hypertension (systolic blood pressure ≥160mmHg).  **Primary Neonatal**  Composite of stillbirth, neonatal death (until 28 days post-birth), and NICU admission requiring separation of infant and mother (until 28 days post-birth).  **Secondary Maternal**  *Note: Variables denoted with a * are reported with treatment effect and 95% CI, all others are exploratory only and described with summary statistics*.   - Mean antenatal systolic blood pressure* - New diagnosis of preeclampsia* - Severe maternal morbidity (fullPIERS consensus definition)* - Discontinuation of allocated antihypertensive* - Undesirable effects of allocated antihypertensive* - Maternal death* - Indicated birth (induction of PROM)* - Mean antenatal diastolic blood pressure - Proportion of days with antenatal systolic blood pressure ≥140mmHg - Proportion of days with antenatal diastolic blood pressure ≥90mmHg - Diagnosis of eclampsia - Diagnosis of HELLP syndrome - Placental abruption - Components of severe maternal morbidity - Maternal stroke - Prescription of additional antihypertensive drugs - Prescription of alternative antihypertensive drugs - Time from randomization to first discontinuation of allocated antihypertensive - Total number of antenatal hospital inpatient days - Treatment satisfaction - Beliefs about allocated antihypertensive drug - Adherence to allocated antihypertensive drug - Mode of onset of birth   **Secondary Neonatal**  *Note: Variables denoted with a * are reported with treatment effect and 95% CI, all others are exploratory only and described with summary statistics*.   - Major congenital anomaly (as defined by EURO-CAT)* - Birthweight centile* - Need for treatment for neonatal hypoglycemia* - Neonatal unit admission (separation of baby from mother)* - Mode of birth* - Gestational age at birth* - Fetal loss <24^+0^ weeks’ gestation - Fetal loss ≥24^+0^ weeks’ gestation (stillbirth) - Known early neonatal death (up to 7 days post-birth) - Known late neonatal death (7-28 days post-birth) - Principal recorded indication for neonatal unit admission - Length of stay in neonatal unit (and level of care) - Indication for mode of birth - Preterm birth (<37 completed weeks) - Preterm birth (<32 completed weeks) - Birthweight - Birthweight SGA (<10^th^ centile) - Umbilical arterial pH<7 at birth - Apgar score 5min post-delivery - Need for additional resuscitation at birth - Need for respiratory support - Type of respiratory support needed - Type of treatment for hypoglycemia - Lowest blood glucose measurement within 48 hours post-birth - Intracranial hemorrhage - Neonatal seizures - Necrotizing enterocolitis | **Primary Maternal**  Our primary outcome will be a composite of severe maternal morbidity determined by an expert panel, comprising:   - Maternal mortality (all cause) - Eclampsia - HELLP syndrome - Stroke - Cortical blindness - Retinal detachment - Pulmonary oedema - Placental abruption - Liver rupture - Need for dialysis - Need for extracorporeal membrane oxygenation (ECMO)   *Note: We do not have reliable ascertainment of ICU/HDU admission data. By instead including only severe morbidities which can reasonably be attributed to hypertensive disorders, we will provide a more accurate picture of the effect of disease-modifying drugs.*  **Primary Perinatal**  Our primary perinatal outcome will be a composite outcome determined by expert consensus. This will comprise.   - Stillbirth (fetal death ≥20 weeks’ gestation) - Neonatal death (death within 28 days of birth) - Severe neonatal morbidity, including:   - Bacterial sepsis   - Birthweight < 3^rd^ centile   - Cardiac arrest   - Hypoxic-ischemic encephalopathy (HIE)   - Intracranial hemorrhage   - Necrotizing enterocolitis   - Neonatal asphyxia   - Neonatal seizures   - Requirement for intubation or mechanical ventilation   - Requirement for resuscitation (mechanical or non-mechanical)   *Note: We do not have reliable ascertainment of NICU admission data. Many infants who are born following hypertensive pregnancies will be admitted to NICU without any other severe morbidities. By instead including only diagnosed severe morbidities, we will provide a more accurate picture of the effect of disease-modifying drugs.*  **Secondary Maternal**  *Note: Variables denoted with a * are reported with treatment effect and 95% CI, all others are exploratory only and described with summary statistics*.   - Pregnancy prolongation (time from first antihypertensive dispensation to birth)* - Need for additional antihypertensive(s)* - Individual components of the primary composite outcome - Disease progression (new diagnosis of preeclampsia after randomization)   **Secondary Perinatal**  *Note: Variables denoted with a * are reported with treatment effect and 95% CI, all others are exploratory only and described with summary statistics*. *** Indicates core secondary outcome.*   - Preterm birth (<37; <34; <32; and <28 weeks’ gestation)** - Major congenital anomaly (as defined by EURO-CAT)* - Neonatal hypoglycemia* - Respiratory distress - Neonatal hypothermia - Individual components of primary composite outcome - Birthweight <10^th^ centile |

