**Define treatment strategy (exposure), assignment procedures, and follow-up period.**

1. The target trial would randomize at the point of diagnosis of a hypertensive disorder of pregnancy (chronic hypertension, gestational hypertension, or preeclampsia). Women would be randomized in a 1:1 ratio to either labetalol or nifedipine. Follow-up would be until 28 days postpartum, and reasons for drop out would include non-adherence to medication, failure to provide consent, unplanned crossover of participants, and random loss to follow up.
2. In the emulated trial, women will be ‘randomized’ at the point of first dispensation of either labetalol or nifedipine at or beyond 11 weeks’ gestation. We will exclude women who were taking both medications prior to 11 weeks’ gestation (unable to be randomized). We will exclude hypertensive women who received neither labetalol or nifedipine (contraindication or non-indication; this cohort will be described). We will also exclude women without hypertension who received labetalol or nifedipine (this cohort will be described).

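### The selection model and both balance tables leave out gestational age at first dispensation, a measured baseline variable that fixes which preterm outcomes can still occur

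*SAP*

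**What the plan says.** The SAP's section on developing the causal model lists, under "Covariates to be included in the selection model", hypertension type, diabetes, plurality, renal disease, autoimmune disease, smoking, body mass index, IVF/ART, SEIFA quintile, maternal age and, for neonatal outcomes, mode of birth. The same section sets the rule for candidates: "All potential confounders are pre-exposure or at exposure".

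The Target Trial Emulation table places assignment "at point of first dispensation of labetalol or nifedipine during the study period", with a window of 11+0 to 36+6 weeks. It gives follow-up as "From 11 weeks’ gestation until 28 days post-birth", which is one start for everyone whenever treatment began.

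The plan gives start gestation weight in several other places:
- Part One lists "Gestation at commencement of treatment" among the maternal baseline characteristics, in three bands.
- The target trial population is described as women "requiring antihypertensive medication at gestational age 11^+0^-19^+6^; 20^+0^-27^+6^; and 28^+0^-36^+6".
- Part Three makes timing of randomization a subgroup factor.
- A starred secondary outcome in the emulation table is measured from the start of treatment: "Pregnancy prolongation (time from first antihypertensive dispensation to birth").

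On earlier treatment, the section defining the treatment strategy says "We will exclude women who were taking both medications prior to 11 weeks’ gestation (unable to be randomized"). Women who used only one of the two drugs before 11 weeks stay in.

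**The concern.** Gestational age at first dispensation is known at exposure, so it meets the plan's own rule for a candidate confounder. It is closely tied to the perinatal outcomes. A woman who starts at 28 weeks or later cannot have a birth before 28 weeks, and the same holds for the 32- and 34-week cut-offs. Stillbirth, part of the primary perinatal composite, can only be counted after treatment has started. Pregnancy prolongation is gestation at birth minus gestation at start.

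The causal reading rests on conditional exchangeability, as the SAP's section on causal contrasts states. If prescribers tended to choose one drug earlier in pregnancy, weighting on the listed covariates would not remove that difference, except as far as those covariates track it. The reported balance would not reveal it either.

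Earlier treatment is a related gap. Because only users of both drugs are excluded, a repeat supply after 11 weeks counts as assignment. A woman on labetalol before 11 weeks whose first later supply is nifedipine counts as starting nifedipine. The crossover definition covers only 11 to 36 weeks, so it does not flag her.

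**Working it through.** **1. Is the variable anywhere in the selection model?**

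| Place in the SAP | Start gestation present? |
| --- | --- |
| Selection-model covariate list (11 entries) | No |
| Balance table, maternal primary model | No |
| Balance table, neonatal primary model | No |
| Part One baseline table | Yes, three bands |
| Target trial population | Yes, three bands |
| Part Three subgroups | Yes, three bands |

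The balance tables do not match the list exactly. They add parity, pool the comorbidities, and the neonatal table has no mode of birth. Start gestation is in neither version.

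**2. Do the reported balance tests help?** The stated results are chi2(11) = 17.67, p = 0.0894, and chi2(10) = 15.23, p = 0.1236. Recomputed upper tails are 0.0896 and 0.1239, agreeing to about 0.0003. The tests concern variables in the model and say nothing about one left out.

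**3. The yardstick.** The Anticipated Sample Size section states detectable differences of 3.0 points (maternal) and 5.6 points (neonatal), from about 7,500 women split 90:10, or about 6,750 and 750. These cannot be reproduced as a check, because alpha, power and base rates are not given. Assuming two-sided 0.05 and an increase on nifedipine, at 90% power 3.0 points fits a labetalol risk of about 5% and 5.6 points fits about 26%. The figures serve below only as a scale.

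**4. Possible size for a risk difference (assumed inputs).** With early and late starters as two strata and no drug effect,

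bias = (between-arm difference in share of early starters remaining after weighting) × (early risk − late risk).

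| Imbalance, points | Gap 5 | Gap 10 | Gap 20 | Gap 30 |
| --- | --- | --- | --- | --- |
| 5 | 0.25 | 0.5 | 1.0 | 1.5 |
| 10 | 0.5 | 1.0 | 2.0 | 3.0 |
| 15 | 0.75 | 1.5 | 3.0 | 4.5 |
| 20 | 1.0 | 2.0 | 4.0 | 6.0 |

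The range is 0.25 to 6.0 points. To judge plausibility, compare standardized differences with the largest raw values in the SAP's tables, 0.1759 (maternal) and 0.1889 (neonatal), both for ART/IVF conception:
- 30% v 50% early starters: 0.20 / √((0.21 + 0.25)/2) = 0.42, more than twice any raw value shown.
- From a 30% share, a standardized difference of 0.1759 is a shift of 8.3 points. The bias is then 0.083 × 5 = 0.4 to 0.083 × 30 = 2.5 points.

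**5. Birth before 28 weeks (assumed shares).** Only women who start before 28 weeks can have this outcome. If their risk is the same in both arms, the relative risk is simply the ratio of the shares:
- 30% v 25%: 0.25/0.30 = 0.83; 30% v 35%: 0.35/0.30 = 1.17.
- 30% v 20%: 0.20/0.30 = 0.67; 30% v 40%: 0.40/0.30 = 1.33.

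A 5-point shift here is a standardized difference of about 0.11 (0.05/√((0.21 + 0.1875)/2)), within the range of the raw values in the tables.

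**6. Pregnancy prolongation.** With equal mean gestation at birth, each week of difference in mean start produces a 7-day apparent effect. This is an identity, not evidence that the arms differ.

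**The case against.** Several points on the other side have force.

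- **No imbalance is shown.** A reader might infer that the arms have different time zeros and that exchangeability fails. The document does not support that. One time-zero rule applies to both arms, and no table gives start gestation by drug. This stands, and it limits the claim to a conditional one.
- **The outcome model may already hold it.** The estimator is doubly robust, and the outcome-model covariates come from DAGs whose figures are not available here. A correctly specified outcome model containing start gestation could protect the estimate. The omission is therefore shown for the selection model only. Double robustness does not help if the variable is missing from both submodels.
- **The exposure model also takes the minimization variables.** The SAP does not list them in full. The balance tables still show no gestation term.
- **Part Three analyses by timing of randomization.** Comparison within bands does limit this confounding, but only in subgroups with wide bands. It leaves the primary effect as it is.
- **Hypertension type is adjusted for** and plausibly tracks start gestation. It would reduce the bias to an unknown extent.
- **Prolongation may not be an effect outcome.** It is starred in the emulation table but absent from the maternal effect-estimate list in the outcome definitions.
- **Retaining users of one drug matches the target trial,** which also excludes only women on both. That is fair on eligibility. In a trial, however, randomization breaks the link between earlier drug and assigned drug, and here nothing does. Adding prior use to the propensity model is not a clean answer: if it nearly fixes the next drug, propensities approach 0 or 1, with only about 750 nifedipine users.

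A reader might also want birth year added, given the span 2009–2020. Nothing in the document indicates that drug choice or outcome risk changed over those years, so it is not part of this point.

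**Conclusion.** The concern holds in a limited form. The stated selection model and the balance checks of both primary models omit gestational age at first dispensation, a measured variable that the plan itself treats as baseline information. If it differs by drug and the outcome model does not carry it, the primary average treatment effect and the preterm and prolongation effects are confounded.

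Neither size nor direction can be known from the document. The range of 0.25 to 6.0 points rests wholly on assumed imbalances and risk gaps. Its upper end needs an imbalance well beyond any raw difference the SAP reports. An imbalance like the largest raw maternal one gives about 0.4 to 2.5 points. The relative risk for birth before 28 weeks is more sensitive, since a 5-point shift alone moves it to 0.83 or 1.17.

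The handling of earlier single-drug use is a second, smaller gap, best met by restriction.

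**What to change.** 1. Add gestational age at first dispensation to the selection model, as a spline or at least in the three bands. The plan's own rule then brings it into the imputation model. Add it to the outcome model if it is not already there, and list that model's covariates in the text.
2. Report its distribution by drug and its standardized difference before and after weighting, for both primary models. If the variable is deliberately left out, state why.
3. Add a sensitivity analysis restricted to women with no dispensing of either drug before 11 weeks. Do not rely on prior use as a propensity covariate, because of the strain on positivity.
4. If bands are used, reconcile the last one: Part Three ends it at 36+0, while the emulation table and Part One end it at 36+6.

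The cost is SAP wording and a rerun of the models. The dispensing records come from the PBS linkage and the birth data from the VPDC, so no new data are needed. Weights will be slightly more variable, and the restricted analysis will be smaller by a number the document does not give.

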**DATA SOURCES**

1. Victorian Perinatal Data Collection (VPDC) and Births, Deaths, and Marriages Registry (BDM)

The VPDC contains comprehensive clinical data for every birth occurring in Victoria. This includes maternal, pregnancy, and infant characteristics and clinical outcomes. This dataset has been used to identify women who gave birth between **2009-2020** and their children. The VPDC has been validated with data from Births, Deaths and Marriages to ensure accuracy. From these datasets, we will ascertain key maternal and neonatal demographics and outcomes.

1. Pharmaceutical Benefits Scheme (PBS)

Many prescription medications are subsidized for Australian citizens under the Pharmaceutical Benefits Scheme, and each prescription medicine that is claimed under this scheme is contained within the PBS data collection. This dataset will be used to identify all women who were prescribed and dispensed labetalol or nifedipine during their pregnancies within the study period.

1. Victorian Admitted Episodes Dataset (VAED) and Victorian Emergency Minimum Dataset (VEMD)

The VAED collects data on all admitted patients from Victorian public and private hospitals. This includes information on presentations, diagnoses, and utilization of healthcare services. The VEMD collects detailed clinical information on all presentations within Victorian emergency departments, including the nature of illnesses/injuries, diagnoses, and transfers. The VEMD and VAED will be used to determine additional maternal and offspring demographics and health outcomes, which may not be included within the VPDC.

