**Outcome definitions – primary and secondary outcomes.**

1. In the target trial, the **primary maternal outcome** is severe hypertension (systolic blood pressure ≥160mmHg). We do not have reliable access to blood pressure measurements; however, our much larger sample size allows us to investigate downstream effects of severe hypertension (severe morbidity). Therefore, the primary maternal outcome will be a composite comprising:
   1. Maternal mortality (all cause) (yes/no)
   2. Eclampsia (yes/no)
   3. HELLP syndrome (yes/no)
   4. Stroke (yes/no)
   5. Cortical blindness (yes/no)
   6. Retinal detachment (yes/no)
   7. Pulmonary oedema (yes/no)
   8. Placental abruption (yes/no)
   9. Liver rupture (yes/no)
   10. Need for dialysis (yes/no)
   11. Need for extracorporeal membrane oxygenation (ECMO) (yes/no)
2. In the target trial, the **primary perinatal outcome** is a composite of stillbirth (≥20 weeks’ gestation), neonatal death (≤28 days post-birth), and neonatal unit admission requiring separation of the infant and mother. We will maintain this outcome by reporting a primary perinatal outcome comprising:
   1. Stillbirth ≥ 20 weeks’ gestation (yes/no)
   2. Neonatal death ≤ 28 days post-birth (yes/no)
   3. Severe neonatal morbidity, comprising:
      1. Neonatal seizures (yes/no)
      2. Necrotizing enterocolitis (yes/no)
      3. Hypoxic-ischemic encephalopathy (yes/no)
      4. Birthweight <3^rd^ centile (yes/no)
      5. Bacterial sepsis (yes/no)
      6. Intracranial hemorrhage (yes/no)
      7. Neonatal asphyxia
      8. Cardiac arrest (yes/no)
      9. Requirement for mechanical or non-mechanical resuscitation (yes/no)
      10. Requirement for intubation or mechanical ventilation (yes/no)
3. In the target trial, there were several **secondary maternal outcomes** (see *Target Trial Emulation* Table Sfor full list). As these secondary outcomes are largely accounted for in our primary composite outcome, we will report the following secondary outcomes with treatment effect and 95% confidence intervals (CI):
   1. Need for additional antihypertensives (yes/no)
   2. Progression from gestational hypertension to preeclampsia (yes/no)

Additionally, the following outcomes will also be reported in an exploratory capacity (i.e., with summary statistics only):

1. Individual components of the primary outcome (all reported as yes/no)
2. Hospital admission prior to 37 weeks’ gestation (yes/no)

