**Causal contrasts of interest**

1. **Estimand**

**Maternal outcomes** – relative risk (RR) and risk difference (RD) of primary composite outcome and pre-specified (*) secondary outcomes (ATE RR, 95% CI).

**Neonatal outcomes** – relative risk (RR) and risk difference (RD) of primary composite outcome and pre-specified (*) secondary outcomes (ATE RR, 95% CI).

In the Giant PANDA RCT, the primary neonatal binary outcome is estimated using a type of logistic regression (log-binomial) model. We will use a logistic regression model with robust standard errors (to adjust for maternal clustering). This model provides predictive probabilities that are then used to calculate both the between exposure difference (RD) and relative risk (RR) for all binary and highlighted (*) secondary outcomes.

In our emulated target trial, the estimand is the average treatment effect (ATE) between exposures, presented using both RD and RR metrics. Within the potential outcomes framework, a causal interpretation can be made under the assumptions of counterfactual consistency, ignorability (conditional exchangeability), and positivity. Counterfactual consistency means that the definition of exposure is consistent for all individuals. Ignorability states that treatment assignment can be considered exchangeable (i.e. as if the assignment was randomized) after controlling for, or conditioning on, a set of covariates. This implies that there are no important unmeasured confounders, an untestable assertion. The positivity assumption means that, for all observations, the conditional probability of being exposed and of not being exposed (receiving treatment or not receiving treatment) are both greater than zero.

1. **Estimators**

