**Details of primary analysis models**

1) Maternal primary analysis model: Propensity score covariate balance assessment, pooled across all imputations and bootstraps

| **Variable** | **Standardised Differences** | |
| --- | --- | --- |
|  | **Raw** | **Weighted** |
| Hypertensive subtype |  |  |
| *Gestational hypertension (ref)* | – | – |
| *Chronic hypertension* | 0.0536 | 0.0046 |
| *Preeclampsia* | 0.1222 | 0.0058 |
| Maternal comorbidities |  |  |
| *No (Ref)* | – | – |
| *Yes* | 0.1745 | 0.0075 |
| Parity |  |  |
| *Multiparous (Ref)* | – | – |
| *Nulliparous* | 0.1103 | 0.0370 |
| Smoking in pregnancy |  |  |
| *No (Ref)* | – | – |
| *Yes* | 0.0062 | 0.0124 |
| Plurality |  |  |
| *Singleton (Ref)* | – | – |
| *Twins or higher order* | 0.0666 | -0.0051 |
| ART/IVF Conception |  |  |
| *No (Ref)* | – | – |
| *Yes* | 0.1759 | -0.0057 |
| SEIFA Quintile |  |  |
| *1 (Ref)* | – | – |
| *2* | -0.0095 | -0.0123 |
| *3* | -0.0933 | -0.0143 |
| *4* | 0.0299 | -0.0007 |
| *5* | 0.1331 | 0.0153 |
| Maternal age | 0.1623 | 0.0012 |
| Maternal body mass index | -0.0366 | 0.0193 |

Test of overidentifying restrictions: chi2(11) = 17.67

Prob > chi2 = 0.0894

Covariates are balanced.

1. Neonatal primary analysis model: Propensity score covariate balance assessment, pooled across all imputations and bootstraps

| **Variable** | **Standardised Differences** | |
| --- | --- | --- |
|  | **Raw** | **Weighted** |
| Hypertensive subtype |  |  |
| *Gestational hypertension (ref)* | – | – |
| *Chronic hypertension* | 0.0459 | 0.0053 |
| *Preeclampsia* | 0.1419 | 0.0003 |
| Maternal comorbidities |  |  |
| *No (Ref)* | – | – |
| *Yes* | 0.1675 | 0.0083 |
| Parity |  |  |
| *Multiparous (Ref)* | – | – |
| *Nulliparous* | 0.0940 | 0.0413 |
| Smoking in pregnancy |  |  |
| *No (Ref)* | – | – |
| *Yes* | 0.0081 | 0.0132 |
| Plurality |  |  |
| *Singleton (Ref)* | – | – |
| *Twins or higher order* | 0.0988 | -0.0101 |
| ART/IVF Conception |  |  |
| *No (Ref)* | – | – |
| *Yes* | 0.1889 | -0.0100 |
| SEIFA Quintile |  |  |
| *1 (Ref)* | – | – |
| *2* | -0.0174 | -0.0108 |
| *3* | -0.0936 | -0.0136 |
| *4* | 0.0289 | -0.0027 |
| *5* | 0.1465 | 0.0132 |
| Maternal age | 0.1702 | -0.0006 |
| Maternal body mass index | -0.0260 | 0.0155 |

Test of overidentifying restrictions: chi2(10) = 15.23

Prob > chi2 = 0.1236

Covariates are balanced.

1. Propensity score overlap plots for primary maternal and neonatal analyses, across all imputations (M=0, M=1, M=2)

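### The adjustment set captures severity only through diagnosis class and obstetric history only through parity, and no bias analysis bounds the residual confounding

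*SAP*

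**What the plan says.** The SAP section on developing a causal model with DAGs gives eleven items under "Covariates to be included in the selection model". They are type of hypertension, diabetes, plurality, renal disease, autoimmune disease, smoking, BMI, IVF/ART conception, SEIFA quintile, age and, for neonatal outcomes, mode of birth. The one item on disease state is "Type of hypertension (gestational hypertension, chronic hypertension, preeclampsia"). The section adds that "All potential confounders are pre-exposure or at exposure".

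The balance tables under Details of primary analysis models show a slightly different fitted set, with comorbidities grouped and parity added. In the maternal model the raw and weighted standardised differences are "Preeclampsia* | 0.1222 | 0.0058" for preeclampsia and "Nulliparous* | 0.1103 | 0.0370" for parity.

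Under Outcome definitions the SAP concedes: "We do not have reliable access to blood pressure measurements". Under Causal contrasts of interest it says of ignorability: "This implies that there are no important unmeasured confounders, an untestable assertion".

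On the hospital admissions dataset, Data Sources says: "This includes information on presentations, diagnoses, and utilization of healthcare services". Gestation at commencement of treatment is derived for the Part One table and used as a subgroup in Part Three. Hospital admission before 37 weeks appears only as an exploratory outcome. Neither is an adjustment variable.

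**The concern.** The SAP presents its maternal composite as a set of downstream consequences of severe hypertension, so severity when the drug is first dispensed is a natural cause of the outcome. If it also influences which drug is chosen, it confounds both primary comparisons. Diagnosis class separates preeclampsia from gestational and chronic hypertension but does not grade severity within a class. Parity records whether there was an earlier birth, not whether it involved preeclampsia, stillbirth or severe growth restriction.

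Comparing estimators does not help. IPW, regression adjustment, IPWRA and TMLE all rely on the same exchangeability assumption given the same kind of covariates, so agreement among them is not evidence that the assumption holds. Good weighted balance on the listed variables says nothing about an unlisted one. The plan includes no E-value, negative control or bias-factor array. At stake is whether a difference in who was given nifedipine is reported as an effect of nifedipine.

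**Working it through.** **Is drug choice related to measured risk?** Yes, modestly. Raw standardised differences (maternal, neonatal model) are 0.1222 and 0.1419 for preeclampsia, 0.1745 and 0.1675 for comorbidities, and 0.1759 and 0.1889 for ART/IVF. The last, 0.1889, is the largest raw value in either table. This makes residual imbalance in severity plausible but does not prove it.

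**Baseline risks.** Anticipated Sample Size gives about 7,500 women split 90:10 (6,750 and 750) and detectable differences of 3.0 points (maternal) and 5.6 points (neonatal). It gives no base rate, power or alpha, so these figures cannot be reproduced uniquely. At two-sided 0.05, a 5% labetalol risk gives 89.9% power for a 3.0-point increase, and a 25% risk gives 90.5% for a 5.6-point increase. I use 5% and 25% as assumptions that fit the stated figures.

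**Bias model (assumed inputs).** There is no true effect. A binary severity marker U, independent of the adjusted covariates, has prevalence q0 = 0.20 with labetalol and q1 with nifedipine, and a risk ratio R of 2 or 3.

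1. Choose q1 to match a standardised difference d = (q1 − q0) / √{[q1(1 − q1) + q0(1 − q0)]/2}. For d = 0.1222, q1 = 0.251. For d = 0.1419, q1 = 0.2595.
2. Spurious RR = [1 + q1(R − 1)] / [1 + q0(R − 1)]. The lowest value is 1.251/1.2 = 1.04 (d = 0.1222, R = 2). The highest is 1.519/1.4 = 1.085 (d = 0.1419, R = 3).
3. Spurious RD = p0 × (spurious RR − 1), where p0 is the labetalol risk. At 25% this is 1.1 to 2.1 points. At 5% it is 0.2 to 0.4 points.
4. False rejection comes from a two-sided 5% pooled two-proportion z test with 750 against 6,750.

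| Assumed imbalance in U | R | Spurious RR | Perinatal RD at 25% | False rejection | Maternal RD at 5% | False rejection |
| --- | --- | --- | --- | --- | --- | --- |
| Raw preeclampsia size (0.12–0.14) | 2–3 | 1.04–1.09 | 1.1–2.1 points | 10–25% | 0.2–0.4 points | 6–9% |
| 30% v 20% (0.232) | 2 | 1.08 | 2.1 points | 24% | 0.4 points | 9% |
| 40% v 20% (0.447) | 2–3 | 1.17–1.29 | 4.2–7.1 points | 69–98% | 0.8–1.4 points | 18–40% |

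The test ignores weighting and clustering, so the rejection rates are approximate. If labetalol users were the more severe group, the bias has the opposite sign.

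**The case against.** The strongest reply is that severity is not ignored. Diagnosis class is a coarse severity marker, and weighting balances it well (preeclampsia 0.1222 to 0.0058 in the maternal model). Subgroups by hypertensive type and by timing of first dispensation are planned. The SAP states its identifying assumption openly, and it cannot adjust for blood pressure that it does not hold. The DAG figures are not available in the text, so severity may be drawn there as an unmeasured node. All of this stands, and it limits the claim. It does not supply a within-class measure or a bound.

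A reader might infer that severity confounding passes directly into both primary ATEs and could by itself produce a significant result most of the time. The documents do not support that. The 40% v 20% row needs a standardised difference of 0.447, about 2.4 times the largest raw imbalance reported (0.447/0.1889). Even 30% v 20% exceeds every reported value. The formula also needs the imbalance that remains within diagnosis class and given the other covariates, which is not known. Unmeasured severity could be more imbalanced than the measured factors, but nothing in the SAP shows it.

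Feasibility is also uncertain. The SAP does not state the look-back of the hospital data or how precisely diagnoses can be dated against dispensing. Births before 2009 fall outside the dataset.

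**Conclusion.** The point holds in a limited form. The adjustment set grades severity only by diagnosis class, and obstetric history enters only as parity, which is in the fitted models but missing from the covariate list. No quantitative check is planned on the assumption that carries the causal claim. Residual confounding by severity is plausible and unbounded, and the documents establish neither its size nor its direction.

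If the residual imbalance matches the raw preeclampsia difference, the perinatal bias is about 1 to 2 points against a stated detectable difference of 5.6, with false rejection of 10 to 25%. The maternal bias is 0.2 to 0.4 points against 3.0, with rejection close to nominal. These figures rest on the assumed 20% prevalence, risk ratio of 2 to 3, and baselines of 25% and 5%. Only under the much larger imbalance does the perinatal bias approach or exceed the detectable difference. It would go too far to infer that the primary results are invalid. The supported conclusion is that the plan lacks a cheap safeguard, more important for the perinatal outcome than for the maternal one.

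**What to change.** Add to the covariate list, the exposure and outcome models (and so the imputation model) and the balance tables whichever of these the linked data support, using only information dated before first dispensation:

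- gestation at first dispensation, which the SAP already derives
- hypertension-related admission or emergency presentation before first dispensation
- preeclampsia, stillbirth or birthweight below the 3rd centile in an earlier linked birth, with nulliparous women kept separate from multiparous women who have no linked earlier birth.

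State the look-back, and state any proxy that proves infeasible. Add parity to the covariate list so that it agrees with the fitted models.

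For both primary ATEs, report a bias analysis, for example an E-value for the estimate and the confidence limit, or a bias-factor array like the one above, and interpret the results in its light. Do not make causal wording conditional on the E-value. When the interval includes 1, the E-value for the limit is 1, so such a rule would fail every null result automatically.

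The cost is SAP wording and a few variables derived from data already linked. The bias analysis needs no new data. The downsides are somewhat more variable weights with only about 750 nifedipine users, an incomplete look-back, and proxies that capture severity only in part. Because the SAP already shows fitted balance tables, label the additions as later changes and report the current model beside the extended one.
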